### Blinding

Blinding of participants and pharmacists is not possible because of the nature of the intervention.

#### *Control group: usual care (Routine dispensing), verbal and written education*

Because there is no blinding, there is no ‘placebo’ treatment. Patients who meet the inclusion criteria will be informed about the study and they will be registered after their signed authorization. The control group (patients and their families) will receive usual care as well as verbal and written information provided by the pharmacist (routine dispensing, including oral counseling regarding drugs). The written material is about mental health (MH) and BD, with information focusing on the importance of adhering to pharmacological and non-pharmacological interventions to achieve treatment goals. Randomization will take place during week zero (baseline) and patients will meet again with the pharmacist every three months (3, 6, 9, and 12 months). At each appointment, variables related to the primary (number of hospitalizations, emergency service consultations, unscheduled outpatient visits) and secondary outcomes (effectiveness, safety, adherence, and quality of life) will be assessed. In addition, patients will fill out a BD knowledge questionnaire every 3 months.

### Intervention design

#### *Intervention group: the Dader Method for pharmaceutical care*

The Dader Method for pharmaceutical care is a systematic process developed by the Research Group of Pharmaceutical Care at the University of Granada, Spain [16]. The intervention is based on the use of pharmacotherapy records, evaluation of an assessment form that includes BD-I and the drugs used to treat this medical problem, and their assessment on a specific date. This assessment is used to identify: (1) any potential or actual patient health outcomes that are not consistent with the objectives of pharmacotherapy and are associated with the use of medicines (negative outcomes associated with medication (NOM)); and (2) situations in which the use of medicines caused or may cause the appearance of a NOM (drug-related problems (DRP)) [14]. Once the relevant problems are identified, the necessary interventions to patients or to physicians are carried out to solve the identified NOM and are followed by a subsequent assessment of the achieved outcomes. There is one pharmacist who is trained to perform the Dader Method of pharmacotherapy follow-up. Figure 1 shows the general study process. In the intervention group, the pharmacist is in charge of doing the following:

**Figure 1 F1:**
[figure not shown]
**General overview of EMDADER-TAB**^**a **^**study. **^a^EMDADER-TAB: Efecto del Método Dader de Seguimiento Farmacoterapéutico en pacientes con Trastorno Afectivo Bipolar I. (Effectiveness of Dader Method for pharmaceutical care in patients with bipolar I disorder]. ^b^The randomization takes place during week zero (baseline) and, during the first 20 days, the pharmacist will reinforce the information related to treatment adherence and ask the patient and his relatives for some criteria that will allow assessing treatment effectiveness and safety. In addition, the pharmacist will make two phone calls (week 1 and 3 from baseline) and a home visit (week 2 from baseline) to assess the variables related to the primary (number of hospitalizations, emergency service consultations, unscheduled outpatient visits) and secondary outcomes (effectiveness, safety, adherence, quality of life). Patients will meet again with the pharmacist every 3 months (3, 6, 9, and 12 months).

1. Developing the first assessment form: data related to mental medical problems are obtained by interviewing the patient, and using information from the drug and clinical records, prescriptions, other records (mainly drug history), and clinical laboratory tests that patients bring in the interview. Health problems (start date, whether it is controlled or not), drugs (start date, active principles, therapeutic strategy, dosage regimen and form of administration, previously used drugs, whether the patient uses the drugs or not, and knowledge of the drugs), patient expectations, lifestyle habits, and demographic data are registered in the assessment form, as well as other health problems with medical diagnosis. The data collected are used to complete the assessment form, which is interpreted and evaluated once all the necessary information is added. The key element to completing the assessment form is the pairing of health problems with the current drug therapy, which provides a global view of the patient’s health status and its relationship with the drugs used.

2. Evaluation and identification of suspected NOM: the collected information is used to study the health problems and drug treatment for subsequent evaluation, based on a literature review of the health problems and pharmacotherapy. The aim of this stage is to assess whether the desired treatment goals are achieved or not. The pharmacist must proceed with the overall patient’s assessment, in the identification and classification of suspected NOM or the possible risk of suffering from a DRP based on the conditions of need, effectiveness, and safety of drug therapy. For patients whose goals have not been achieved yet, the pharmacist will develop therapeutic plans that include interventions aiming to achieve the desired clinical outcome.

3. Intervention to prevent or resolve a NOM (intervention phase): this phase aims to resolve the NOM and DRP detected, and also to establish a monitoring plan to avoid the appearance of a new NOM. Once the pharmacist identifies concerns about the medical problems and current drug therapy, she/he interpreted and analyzed this information in the context of the clinical condition illustrated by the assessment form. If the aim of the intervention is to modify a problem with lifestyle or with the use of a medication, the recipient of the intervention is the patient or a relative. If the aim of the intervention is to modify drug therapy in a quantitative way (for example, modifying dosage or frequency) or in a qualitative way (for example, adding or changing any drug), the recipient of the intervention will be the physician. The intervention ends by verifying if the reason for the intervention has been solved or not and if enough time has been allowed to assess the intervention. The interdisciplinary teamwork should also be integrated in the intervention phase to combine efforts in treating the disease.

4. New assessment form of the patient: completion of an intervention should have generated a change in the patient’s assessment. The therapeutic plan is carried out depending on whether a NOM still exists or not, for example: informing the physician that mood stabilizers and antipsychotics medication are not effective and that the patient therefore may need a modification in drug therapy. Also, plan modifications are made when patients do not achieve positive results. In cases where the intervention needs to continue, an appropriate monitoring plan should be carried out according to the characteristics of the patient’s problems and idiosyncratic individuals’ situation.

Patients who meet the inclusion criteria will be informed of the study and they are registered after the authorization. In addition, the intervention group, patients and their families, will receive usual care as well as verbal and written information provided by the pharmacist (routine dispensing, including oral counseling regarding drugs). The written material is about MH and BD with information focusing on the importance of adhering to pharmacological and non-pharmacological interventions to achieve treatment goals. The randomization takes place during week zero (baseline), and, during the first 20 days, the pharmacist will reinforce the information related to treatment adherence and ask the patient and his relatives for some criteria that will allow assessing treatment effectiveness and safety. In addition, the pharmacist will make two phone calls (week 1 and 3 from baseline) and a home visit (week 2 from baseline) to assess the variables related to the primary (number of hospitalizations, emergency service consultations, unscheduled outpatient visits) and secondary outcomes (effectiveness, safety, adherence, quality of life). Patients will meet again with the pharmacist every three months (3, 6, 9, and 12 months). In addition, patients will fill a BD knowledge questionnaire every 3 months.

The intervention group patients will be monitored through the Dader Method for pharmaceutical care, over a 12-month follow-up period, to identify, prevent, and resolve drug-related problems with the process (causes) and drug-related problems with the outcome (effects). The strategy will consist of weekly phone calls and appointments with the patient, which, depending on the case, will take place at the patient’s home or at the pharmacist’s office. The pharmacist will inform the psychiatrist responsible for the patient in the case an effectiveness or safety problem related to the drugs is found, and the psychiatrist will determine the process to be followed.

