### Study outcomes

#### *Evaluation/assessment variables/measuring instruments*

The primary outcomes to be measured are: (1) the number of hospitalizations; (2) the number of emergency service consultations; and (3) the number of unscheduled outpatient visits. In addition to the information provided by patients and family members about the primary objective, the pharmacist gets the information from the records of medical history of the patients, provided by SJDC.

The secondary outcomes to be measured are: (1) adherence to treatment through serum lithium levels, serum valproate levels, carbamazepine-serum levels, and by the questionnaire of Morinsky-Green (MG) [21]; (2) life quality through the Quality of Life Scale: The Short Form (36) Health Survey Questionnaire [22]; (3) Clinical Global Impression for Bipolar Modified scale, CGI-BP-M [23]; (4) Young Mania Rating Scale for the evaluation of mania [24]; (5) Hamilton Rating Scale for Depression [25]; (6) drug safety through creatinine, liver transaminases, alkaline phosphatase, complete blood count, fasting glucose, thyroid stimulating hormone levels (TSH), total T4 or total thyroxin levels (T4), weight and cholesterol; (7) problems related to necessity, effectiveness, and security of the pharmacotherapy (NOMs to be identified and measured); (8) drug-related problems in drug therapy effectiveness, and safety; (9) the impact of side effects of antipsychotic drugs on health-related quality of life with a specific self-rated instrument: the ‘Tolerability and quality of Life’ (TOOL) questionnaire [26]; and (10) the patient’s satisfaction with the pharmaceutical care service measured through the patient satisfaction questionnaire on pharmaceutical care [27]. Control and intervention groups will be compared in terms of the proportion of changes from baseline to follow-up at 12 months. The information collected at 3, 6, and 9 months is part of the follow-up period of patients, and these data help to complement the secondary outcomes of the trial. Secondary outcomes will handled in terms of the proportion of changes from baseline to 12 months following.

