The results could be subject to potential biases because: (1) the patients in this study will not be blinded to treatment assignment, and the same pharmacist, who is responsible for collecting trial data, will observe both the control and the intervention group; and (2) control group patients will receive phone calls from the pharmacist, who will encourage their attendance of appointments. These patients will also receive written material and verbal information about BD, MH, and counseling about the importance of adherence to pharmacological and non-pharmacological interventions to achieve therapeutic goals, as requested by the Human Research Ethical Committee in its approval of this research project. The effect of educational written material and the extra attention received by the patients in the usual care group might produce positive outcomes and reduce the magnitude of the differences with the intervention group.

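### Primary events are sought at more contacts in the intervention arm than in control, so events outside the study clinic may be detected unequally; drug-problem outcomes need one common rating procedure.

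*Protocol article*

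**What the plan says.** **Intervention arm.** The Intervention group section, and again the Figure 1 legend, state that "the pharmacist will make two phone calls (week 1 and 3 from baseline) and a home visit (week 2 from baseline) to assess the variables" behind the primary and secondary outcomes. They continue: "Patients will meet again with the pharmacist every three months (3, 6, 9, and 12 months"). The same section then describes follow-up over the year: "The strategy will consist of weekly phone calls and appointments with the patient", at home or at the pharmacist's office.

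**Control arm.** The Control group section says "patients will meet again with the pharmacist every three months (3, 6, 9, and 12 months"), and places the assessment there: "At each appointment, variables related to the primary (number of hospitalizations, emergency service consultations, unscheduled outpatient visits) and secondary outcomes". The Discussion adds that "control group patients will receive phone calls from the pharmacist, who will encourage their attendance of appointments".

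**Common text.** The Data collection section sets evaluation of the study variables at baseline and every 3 months, without distinguishing the arms. Study outcomes names two sources for the primary events: "In addition to the information provided by patients and family members about the primary objective", the pharmacist uses the medical records of the San Juan de Dios Clinic (SJDC).

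**Drug-problem outcomes.** Secondary outcome 7 is "problems related to necessity, effectiveness, and security of the pharmacotherapy (NOMs to be identified and measured"), where NOM means negative outcomes associated with medication. Outcome 8 is drug-related problems. The groups are to be compared on change from baseline to 12 months.

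**The concern.** The two arms do not have the same number of occasions on which a primary event can come to light. For an event recorded at SJDC this matters little, because the record is read for both arms. For an event at another provider, patient or family report is the only route that the article names. SJDC is a psychiatric clinic in La Ceja, and eligible patients live in 17 municipalities, Medellín among them, so events elsewhere are plausible.

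If report is taken within days or weeks in one arm and over three months in the other, fewer outside events may be forgotten in the first. The intervention count would rise relative to control for reasons unrelated to treatment, and a true reduction would look smaller.

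The drug-problem outcomes raise a related difficulty. Finding NOMs and drug-related problems is the purpose of the Dader Method, and no process for finding them is described in control. A between-group comparison could then reflect how hard each arm was searched.

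**Working it through.** **1. Outcome contacts after baseline.** Intervention: 2 calls + 1 home visit + 4 quarterly visits = 7 contacts at which outcomes are expressly assessed. Control: 4. If the weekly calls run all year (an assumption), there are about 52 further contacts at which an event may become known, although outcome collection is not their stated purpose.

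**2. The plan's own figure.** The sample size section assumes 50% against 30% readmission, 95% confidence and 80% power, and states at least 166 patients. With 1:1 allocation the two-sided formula gives 93 per arm (186) without continuity correction and 103 per arm (206) with it. Of the variants tried, only the one-sided formula with correction gives 83 per arm, or 166. The present point does not depend on this. It uses the planned 200, that is 100 per arm, and the two-sided 5% test of the Biostatistical considerations.

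**3. Power with equal detection.** Power = Φ[(d − 1.96·SE0)/SE1], with d = p1 − p2, SE0 = √(2p̄(1 − p̄)/n) and SE1 = √((p1(1 − p1) + p2(1 − p2))/n). For 0.50 and 0.30 with n = 100: SE0 = 0.0693, SE1 = 0.0678, (0.20 − 0.1358)/0.0678 = 0.947, power 82.8%.

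**4. Unequal detection.** Assumed, because the document gives no figures: a share *out* of admissions occurs outside SJDC, quarterly recall finds a share *cap* of these, and the intervention arm misses none. Observed control rate = 0.50 × (1 − out + out × cap); the intervention rate stays at 30%.

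| out | cap | Observed control | Difference | Power |
|---|---|---|---|---|
| 0.2 | 0.7 | 47.0% | 17.0 points | 70% |
| 0.3 | 0.7 | 45.5% | 15.5 points | 62% |
| 0.3 | 0.5 | 42.5% | 12.5 points | 45% |

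With no treatment effect and a true rate of 50% in both arms, the same scenarios give two-sided rejection rates of 7.1%, 9.7% and 18.6% instead of 5%. The excess would point to harm.

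**5. Two ways to equalise detection, same assumptions.** Using both sources at the common visits multiplies both rates by (1 − out + out × cap). Using SJDC records alone multiplies both by (1 − out).

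| out, cap | Both sources, common visits | Power | SJDC records only | Power |
|---|---|---|---|---|
| 0.2, 0.7 | 47.0% v 28.2% | 79% | 40% v 24% | 68% |
| 0.3, 0.7 | 45.5% v 27.3% | 77% | 35% v 21% | 60% |
| 0.3, 0.5 | 42.5% v 25.5% | 72% | 35% v 21% | 60% |

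Both remove the asymmetry. The first keeps more power in every scenario.

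**The case against.** The best defence is that ascertainment is already common where it counts. Data collection gives one quarterly schedule for both arms, and the same two sources apply to all patients. The three extra contacts fall in the first 3 of 52 weeks, a period that the month-3 visit also covers. This limits the problem but does not remove it: the Intervention group section says those contacts are made to assess the primary outcomes, and nothing says which contacts feed the count.

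Several stronger readings are tempting and are not supported:

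- *The weekly calls are outcome collection.* Their stated purpose is to find, prevent and resolve drug-related problems. Events can become known there; the text does not say that they are recorded from there.
- *The unblinded pharmacist decides what counts as an event.* The Discussion says only that the same pharmacist collects the data in both arms. It already admits that potential bias, and the absence of blinding, but not the unequal intensity of assessment.
- *Control patients have no NOM or drug-problem assessment, so these outcomes are meaningless.* That is inferred from silence. The Control group section has secondary outcomes assessed at each appointment; it describes no procedure for these two.

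The magnitude is also open to challenge, and the challenge stands. The shares are assumed. A hospital admission is perhaps the event least easily forgotten. The formula treats each patient as having one admission, whereas a patient with a second, recorded admission would still be counted. Emergency and unscheduled visits, where recall probably matters more, are not modelled.

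**Conclusion.** The point holds as a difference in the opportunity to detect primary events, arising from three sections that need to be reconciled. It concerns mainly events outside SJDC; admissions to SJDC are largely protected by the shared record. Extra detection in the intervention arm would tend to mask benefit, though bias from an unblinded data collector could run either way. The 45% to 70% power range shows what the assumed shares imply and is not an estimate for this trial.

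For NOMs and drug-related problems the conclusion is conditional: the comparison is interpretable if both arms are rated by the same procedure, and the article does not describe one for control.

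A reader might infer that the primary analysis should rest on SJDC records alone, or that satisfaction with the service should be dropped as an outcome. Neither follows. Records alone discard outside events in both arms and, under the first two scenarios, give slightly less power than the unequal detection itself (68% against 70%, 60% against 62%). As for satisfaction, control patients also receive counselling from the pharmacist, and nothing here shows that the outcome is unusable.

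**What to change.** State one ascertainment rule for both arms:

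- **Primary analysis.** Count events from SJDC records for each patient's 12 months, and from patient or family report at the 3-, 6-, 9- and 12-month visits. Flag the source of every event. Do not count an event known only from an intervention call or home visit.
- **Sensitivity analysis.** Repeat the comparison with SJDC-record events alone.
- **NOMs and drug-related problems.** Compare the groups only on ratings made by the same procedure at the common visits in both arms. If that is not done, report them as process measures of the intervention.

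The contacts themselves need not change; only the counting rule does. The cost is wording and one database field. Randomisation began in November 2011, so events already entered need their source coded afterwards. Some real events known only from intervention contacts will be dropped. Some imbalance may remain, because the pharmacist will already know of events when asking at the quarterly visit; the records-only analysis shows whether the conclusion depends on reported events.

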### Study outcomes

#### *Evaluation/assessment variables/measuring instruments*

The primary outcomes to be measured are: (1) the number of hospitalizations; (2) the number of emergency service consultations; and (3) the number of unscheduled outpatient visits. In addition to the information provided by patients and family members about the primary objective, the pharmacist gets the information from the records of medical history of the patients, provided by SJDC.

The secondary outcomes to be measured are: (1) adherence to treatment through serum lithium levels, serum valproate levels, carbamazepine-serum levels, and by the questionnaire of Morinsky-Green (MG) [21]; (2) life quality through the Quality of Life Scale: The Short Form (36) Health Survey Questionnaire [22]; (3) Clinical Global Impression for Bipolar Modified scale, CGI-BP-M [23]; (4) Young Mania Rating Scale for the evaluation of mania [24]; (5) Hamilton Rating Scale for Depression [25]; (6) drug safety through creatinine, liver transaminases, alkaline phosphatase, complete blood count, fasting glucose, thyroid stimulating hormone levels (TSH), total T4 or total thyroxin levels (T4), weight and cholesterol; (7) problems related to necessity, effectiveness, and security of the pharmacotherapy (NOMs to be identified and measured); (8) drug-related problems in drug therapy effectiveness, and safety; (9) the impact of side effects of antipsychotic drugs on health-related quality of life with a specific self-rated instrument: the ‘Tolerability and quality of Life’ (TOOL) questionnaire [26]; and (10) the patient’s satisfaction with the pharmaceutical care service measured through the patient satisfaction questionnaire on pharmaceutical care [27]. Control and intervention groups will be compared in terms of the proportion of changes from baseline to follow-up at 12 months. The information collected at 3, 6, and 9 months is part of the follow-up period of patients, and these data help to complement the secondary outcomes of the trial. Secondary outcomes will handled in terms of the proportion of changes from baseline to 12 months following.

